## Abstract

**Introduction and aims:**

Veno-arterial extracorporeal membrane oxygenation (VA-ECMO) is an increasingly utilized therapeutic choice in patients with cardiogenic shock, however, high complication rate often counteracts with its beneficial cardiopulmonary effects. The assessment of left ventricular (LV) function in key in the management of this population, however, the most commonly used measures of LV performance are substantially load-dependent. Non-invasive myocardial work is a novel LV functional measure which may overcome this limitation and estimate LV function independent of the significantly altered loading conditions of VA-ECMO therapy. The Usefulness of Myocardial Work IndeX in ExtraCorporeal Membrane Oxygenation Patients (MIX-ECMO) study aims to examine the prognostic role of non-invasive myocardial work in VA-ECMO-supported patients.

**Methods:**

The MIX-ECMO is a multicentric, prospective, observational study. We aim to enroll 110 patients 48–72 h after the initiation of VA-ECMO support. The patients will undergo a detailed echocardiographic examination and a central echocardiography core laboratory will quantify conventional LV functional measures and non-invasive myocardial work parameters. The primary endpoint will be failure to wean at 30 days as a composite of cardiovascular mortality, need for long-term mechanical circulatory support or heart transplantation at 30 days, and besides that other secondary objectives will also be investigated. Detailed clinical data will also be collected to compare LV functional measures to parameters with established prognostic role and also to the Survival After Veno-arterial-ECMO (SAVE) score.

**Conclusions:**

The MIX-ECMO study will be the first to determine if non-invasive myocardial work has added prognostic value in patients receiving VA-ECMO support.

## Introduction

Cardiogenic shock (CS) is the most severe form of acute heart failure, defined as a state in which the heart cannot maintain adequate cardiac output even with markedly increased filling pressures (1). A characteristic feature of CS is systemic organ hypoperfusion, resulting in progressive multi-organ failure, and consequently, poor clinical outcome (2). Despite the constant improvements in pharmacological and supportive therapy, CS has an outstandingly high mortality even in the most advanced healthcare systems worldwide (2).

By implementing a simple concept, e.g., artificial replacement of the function of the cardiopulmonary system, Veno-Arterial Extracorporeal Membrane Oxygenation (VA-ECMO) is a distinct approach in the management of cardiogenic shock (3). VA-ECMO support was utilized in various causes of CS. In patients with CS complicating acute coronary syndrome (ACS), it is hypothesized that VA-ECMO enables to “bypass” that critical period during which substantial myocardial stunning is present, however, randomized clinical trials failed to demonstrate improved prognosis compared to conservative therapy (4, 5). VA-ECMO is also frequently used in CS due to non-ischemic causes (6, 7), or failure to weaning from cardiopulmonary bypass in cardiac surgery patients (8). Early VA-ECMO, as extracorporeal cardiopulmonary resuscitation in cardiac arrest patients is an interesting novel concept, and importantly, initial data seem to support its use (4, 9). Despite the recent studies failed to demonstrate consistent improvement in clinical outcomes compared to the conventional therapy (5, 10), VA-ECMO may provide substantial aid to the cardiopulmonary system leading to favourable outcome in well-selected patients, however, we are still lacking criteria for the most optimal candidacy of the therapy and contraindications (e.g., age ≥ 75 years, severe brain injury, malignancy and other conditions limiting life expectancy) are much more defined (11).

Prolonged VA-ECMO has numerous severe complications. Bleeding events are particularly prevalent in this population, often occurring as a life-threatening complication (12, 13). Beyond haemorrhage, thromboembolic events and the higher incidence of infections are also frequently reported. Therefore, the earliest possible weaning from VA-ECMO is an important therapeutic goal.

The reliable measurement of left ventricular (LV) function is one of the cornerstones to assess the possibility of weaning (14). In clinical practice, echocardiography is the most widely used method for monitoring the LV function. However, even recently developed LV functional measures, such as speckle-tracking echocardiography-derived global longitudinal strain (GLS) are highly load-dependent (15). This load-dependency gains particular importance in certain clinical states, and the significantly deranged loading conditions of VA-ECMO therapy is one of the most relevant ones (16).

Non-invasive myocardial work indices are novel echocardiographic parameters which adjust LV deformation to the instantaneous LV pressure, overcoming the load-sensitivity of the traditional LV functional measures (17). Experimental studies demonstrated that myocardial work indices may be reliable markers of LV contractility in animal models of pressure- or volume-overload-induced heart failure (17). These observations may explain why myocardial work markers were shown to be superior prognostic markers in various clinical settings.

We hypothesize that VA-ECMO patients may also benefit from myocardial work-based LV function evaluation and these novel, non-invasive indices of cardiac performance may be robust markers of patient outcome in this population.

## Study objectives

The “usefulness of Myocardial work IndeX in ExtraCorporeal Membrane Oxygenation patients” (MIX-ECMO) study aims to study the association of non-invasive myocardial work indices with outcome in patients undergoing VA-ECMO therapy.

The primary objective measure is the failure to wean, which consists of different clinical outcomes suggesting the inability to free the patient from MCS:
•Failure to wean: Composite of cardiovascular mortality, need for long-term mechanical circulatory support (MCS) or heart transplantation at 30 days

Besides that, secondary objectives will be also investigated to examine all-cause mortality and certain endpoints of organ-failure:

Secondary outcome measures:
•All-cause mortality at 30 days•VA-ECMO-free days at 30 days•Need for renal replacement therapy during intensive care at 30 days•Successful weaning from mechanical ventilation at 30 days•Ventilator-free days at 30 days•Discharge from intensive care unit (ICU) at 30 days•Discharge from hospital at 30 days

## Study design

MIX-ECMO is an investigator-initiated prospective, multicentre observational study enrolling patients in three European investigational Centres. The study will be conducted in accordance with the Helsinki Declaration, the Good Clinical Practice, and the applicable regulatory requirements.

The study is registered on NIH ClinicalTrials.gov (Identifier: NCT05838937).

## Ethical considerations

The MIX-ECMO study will be conducted in accordance with good clinical practice and the Helsinki Declaration. All regulatory and notified body requirements have been met to perform the study. The MIX-ECMO study has been catalogued and authorized by the Hungarian Medical Research Council under number: BMEÜ/4229-1/2022/EKU. Due to the nature of the examined population, most commonly legally eligible relatives are expected to provide their written informed consent prior to enrolment, which will be collected by certified physicians participating in the study.

## Sample size and patient population

Patients undergoing VA-ECMO (regardless of the indication for the therapy) will be enrolled. The initial plan is to enroll patients within 1 year, with no loss to follow-up. Based on a previous VA-ECMO study investigating echocardiographic predictors of outcome (18), we estimated a 92.2% statistical power to detect a 20% effect with respect to the primary composite outcome, by assuming an 30% weaning failure rate in a sample size of 100 patients. Importantly, the feasibility of speckle-tracking analysis with transoesophageal echocardiography (TOE) was previously reported to be 90% (19). Therefore, we aim to enroll 110 subjects, a sample size which exceeds previous cardiac imaging studies of the field able to demonstrate association of echocardiography measures with outcome (18, 20). Both peripherally and centrally cannulated subjects are candidates for participation. Considering that the two populations are typically quite different in terms of indication for the therapy (ACS- or decompensated chronic heart failure-associated CS vs. cardiac surgery population), a balanced enrollment of the two methods will be facilitated by interim assessment at 50% of the enrollment. All LV venting options are eligible for enrollment, however, if utilized, the mode of LV unloading (central left atrial vent, Impella, transaortic LV pigtail catheter etc.) will also be collected. Notably, LV unloading significantly influences ventricular mechanics (21). Still, due to the highly variable institutional practices in terms of LV unloading, the study protocol does not exclude certain techniques.

The study aims to include a broad spectrum of patients; therefore, the exclusion criteria are mainly technical contraindications of the measurements. Patients 18 years or older on VA-ECMO will be enrolled, if TOE is feasible or the transthoracic echo window also enable sufficient image quality for further analysis. The inclusion and exclusion criteria are listed in Table 1.

**Table 1 T1:** Inclusion and exclusion criteria of the study.

Inclusion criteria	Exclusion criteria
Patients 18 years old or older	Younger than 18 years old
Cardiogenic shock refractory to conventional therapy, requiring VA-ECMO implantation	Written informed consent cannot be collected
Written informed consent (most commonly by a legally eligible relative)	Poor transthoracic window and transesophageal echocardiography is contraindicated (e.g., severe pharyngeal or oesophageal bleeding, extreme coagulation derangement)
	Poor echocardiographic window from both transthoracic and transesophageal approach
	Clinical condition at the time of enrollment which squarely indicates therapy limitation and poor short-term outcome (e.g., established diagnosis of severe cerebral damage, severe hemodynamic instability despite MCS and vasoactive therapy)

Importantly, enrollment and the study procedures must take place between 48 and 72 h following the initiation of MCS. The main objectives of the study are depicted in Figure 1.

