## Statistical analysis

The association of conventional measures of LV function, myocardial work and patient outcome will be assessed by logistic regression, and for certain objectives (ventilator free days, VA-ECMO free days) by linear regression. Despite the limited sample size, a large event rate can be expected in most of the outcome measures, potentially enabling multivariate logistic analyses. Collinearity of variables will be tested at each multivariable model by variance inflation factor (excessive if variance inflation factor >3). To examine the potential added prognostic value of myocardial work to other parameters, the constructed multivariable models will be compared based on Akaike Information Criterion (AIC). Receiver operating characteristic (ROC) curves will be calculated to assess the discriminatory power of the relevant parameters with regards to the study endpoints. Youden index will be used to quantify the optimal cutoff points of each parameter. These cutoff values will be used to dichotomize the study population. Outcomes of the dichotomized groups will be visualized using Kaplan-Meier curves and compared by the log-rank test. All statistical analyses will be performed using SPSS Statistics (IBM Software Group, Armonk NY, USA). A *P*-value of <0.05 will be considered statistically significant.

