Recently, other LV functional measures emerged as potential candidates to overcome this issue. Tissue Doppler Imaging-based myocardial velocities and speckle-tracking-derived GLS was shown to be superior markers of LV systolic function with established prognostic value in acute heart failure (30). Nevertheless, even such measures of the LV performance are shown to be highly load-dependent, limiting their comparability in a patient-to-patient basis.

VA-ECMO significantly alters LV load, which hinders the actual contractile state of the chamber: LV unloading may decrease the value of traditional functional measures, while the concomitant increase in LV afterload further deteriorates LV ejection and may obscure an otherwise maintained LV inotropy (21). Notably, methods of LV unloading, such as concomitant Impella support, intra-aortic balloon pump or direct surgical venting have markedly different effect on LV load, further complicating the interpretation of LV function in a VA-ECMO-supported patient (21, 31). Generally, pressure-volume loops are shifted to the left resulting in lower LV volumes and pressures, while Impella also results in significant shortening of the isovolumetric phases. Moreover, LV venting (transaortic pigtail, LA cannula) does not modify LV afterload, on the other hand, Impella and intraortic balloon pump unloads the LV by decreasing the afterload. As a sum of these influencing factors, LV performance during MCS barely represents ventricular function after weaning. Analysis of the Extracorporeal Life Support Organization (ELSO) registry demonstrated that systolic blood pressure during MCS has incremental prognostic value over the SAVE score, showing that pressures generated by the LV are of great importance (32). Therefore, we hypothesize that the integrative assessment of LV function and concomitant pressures may overcome the limitation of conventional LV functional measurements. Similarly, to this concept, a recent study showed that right ventricular GLS-based measures of right ventricle-pulmonary artery coupling are associated with prognosis in VA-ECMO patients (20).

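### Cannulation route is balanced at enrolment but used in none of the stated analyses; adding it as a model term and log-rank stratum is a cheap improvement

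*Protocol article*

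**What the plan says.** Under Sample size and patient population, the protocol article admits both central and peripheral cannulation. It notes that "the two populations are typically quite different in terms of indication for the therapy", contrasting shock from acute coronary syndrome or decompensated chronic heart failure with the cardiac surgery population. As a consequence, "a balanced enrollment of the two methods will be facilitated by interim assessment at 50% of the enrollment".

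Under Statistical analysis it lists:
- logistic regression, and linear regression for ventilator-free and VA-ECMO-free days;
- multivariable logistic models, described as potentially possible, compared by AIC to judge the added value of myocardial work;
- ROC curves for the relevant parameters;
- a Youden cutoff for each parameter, of which it says "These cutoff values will be used to dichotomize the study population";
- Kaplan-Meier curves of the resulting groups, compared by a log-rank test.

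No covariates are named for the multivariable models, and no stratum is named for any analysis. Cannulation route is mentioned only in connection with recruitment.

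**The concern.** The exposure under study is the work index, not the route. Recruiting equal numbers by route sets the proportion of each group in the sample, but it does not make patients with high and low work comparable in route. If one route has both a different typical work index and a different failure rate, an analysis that ignores route mixes the difference between routes with the within-route signal. An association can then be inflated, or a real one diluted. A single cutoff also depends on a case mix that the study itself has steered.

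The article gives some reason to expect each link:
- **Route and outcome.** Route is tied to indication in the sample size section, and the Discussion names underlying aetiology among the components of the SAVE score, which predicts survival.
- **Route and work index.** The sample size section says that unloading alters ventricular mechanics and lists a central left atrial vent among the modes. The Discussion adds that "Impella and intraortic balloon pump unloads the LV by decreasing the afterload", whereas venting does not modify afterload. That unloading mode varies with route is an inference; the article does not say so.

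At stake is the reading of the main objective in Assessment of endpoints, namely whether work indices are better prognostic markers than conventional LV measures.

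**Working it through.** **The plan's own figure.** The only power statement is that "we estimated a 92.2% statistical power to detect a 20% effect with respect to the primary composite outcome". It rests on 100 patients and a failure rate of 30%. Neither the groups compared nor the scale of the effect is defined. Two groups of 50 with a 20-point difference (30% vs 10%, 40% vs 20% or 30% vs 50%) give 53-71% two-sided and at most 81% one-sided, so 92.2% is not reproduced from the stated inputs. This does not bear on the present point, which takes only the 30% rate and the 100 patients from that passage.

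**Inputs from the article.** 100 analysable patients, 30% failure, routes about 1:1, alpha 0.05 (taken as two-sided).
- Events: 100 × 0.30 = 30.
- Per route at equal risk: 50 × 0.30 = 15.
- Per route at 40% and 20%: 50 × 0.40 = 20 and 50 × 0.20 = 10.

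**Assumed inputs, because the article gives none by route.** Work index normal with SD 1 within route and outcome group; mean shift *d* between routes of 0, 0.5 or 1 SD; failure rates of 30/30, 35/25 or 40/20, in either direction.

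**Pooled AUC in closed form.** Let L be the lower-work and H the higher-work route, with failure rates p_L and p_H. Take AUC as the probability that a random non-failure has higher work than a random failure. With equal route sizes:
- share of failures from L: f = p_L / (p_L + p_H);
- share of non-failures from L: g = (1 − p_L) / (2 − p_L − p_H);
- within-route separation for within-route AUC *w*: δ = √2 · Φ⁻¹(w);
- pooled AUC = [f·g + (1−f)(1−g)]·w + f(1−g)·Φ((δ+d)/√2) + (1−f)g·Φ((δ−d)/√2).

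*No within-route association* (w = 0.5, δ = 0), p_L = 0.40, p_H = 0.20: f = 0.667 and g = 0.429. The expression reduces to 0.5 + (f − g)(Φ(d/√2) − 0.5).
- d = 0.5: 0.5 + 0.238 × 0.138 = 0.533.
- d = 1: 0.5 + 0.238 × 0.260 = 0.562.
- If the higher-work route fails more, the mirror images are 0.467 and 0.438.

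*True within-route AUC 0.70* (δ = 1.414 × 0.524 = 0.742), d = 1, so that Φ(1.231) = 0.891 and Φ(−0.183) = 0.427:
- higher-work route fails less: 0.476 × 0.70 + 0.381 × 0.891 + 0.143 × 0.427 = 0.734;
- higher-work route fails more: 0.476 × 0.70 + 0.143 × 0.891 + 0.381 × 0.427 = 0.623;
- equal failure rates: 0.5 × 0.70 + 0.25 × (0.891 + 0.427) = 0.680.

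**Rejection rates by simulation.** 1,500 trials of 100 patients per scenario, comparing a pooled Mann-Whitney test with a route-stratified (van Elteren type) test. The Monte Carlo standard error is √(0.05 × 0.95/1500) = 0.6 points near 5% and √(0.52 × 0.48/1500) = 1.3 points near 52%.

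| Within-route AUC | Shift (SD) | Failure, lower-/higher-work route | Pooled AUC | Pooled rejects | Stratified rejects |
|---|---|---|---|---|---|
| 0.50 | 0 | 40/20 | 0.50 | 5.3% | 5.1% |
| 0.50 | 1 | 30/30 | 0.50 | 5.3% | 5.3% |
| 0.50 | 0.5 | 40/20 | 0.53 | 7.7% | 4.3% |
| 0.50 | 0.5 | 20/40 | 0.47 | 7.1% | 4.9% |
| 0.50 | 1 | 40/20 | 0.56 | 15.0% | 4.9% |
| 0.50 | 1 | 20/40 | 0.44 | 17.5% | 5.6% |
| 0.50 | 1 | 35/25 | 0.53 | 7.9% | 5.3% |
| 0.70 | 1 | 40/20 | 0.73 | 97.1% | 87.1% |
| 0.70 | 1 | 30/30 | 0.68 | 81.4% | 89.3% |
| 0.70 | 1 | 20/40 | 0.62 | 51.7% | 87.9% |

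The simulated AUCs agree with the closed form.

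**The case against.** The case on the other side is substantial.

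- **No figures by route.** A reader might infer that route does confound the stated analyses. The article does not support that. It says only that indications differ, and reports no difference by route in work index or failure rate. If either difference is zero, type I error stays near 5%; a 1 SD shift with equal failure rates only moves the AUC from 0.70 to 0.68. This stands.
- **Adjustment is not ruled out.** The multivariable models compared by AIC could include route. The article is condensed and an analysis plan may list the covariates, so the missing list is not itself a fault. The words pooled and unstratified are this review's reading, not the article's. This stands in part: those models are only potentially planned, and they would not change the ROC, cutoff or log-rank results, which are described for the whole study population.
- **A pooled AUC is legitimate.** In a deliberately broad VA-ECMO population it measures marginal discrimination. This stands, for the mix of routes sampled.
- **The main objective is comparative.** Work is set against EF, GLS, outflow-tract VTI and the SAVE score in the same patients. Route may shift those markers too, and the SAVE score already carries aetiology. The simulation concerns the work-outcome association alone, so a reader should not infer that the comparison between markers has been shown to be biased.
- **Load may matter less than feared.** A second acquisition at support normalised to body surface area reduces differences due to flow, though not those due to venting. The remarks on Impella and balloon pump concern unloading mode, which is not the same as route.

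**Conclusion.** The point holds in a limited form. The article singles out route as a source of heterogeneity and acts on it in recruitment, yet none of the analyses it states uses it. Balanced enrolment does not fill that gap. The size is conditional on unpublished quantities. With a 20-point difference in failure and a 0.5 to 1 SD shift in work, pooled type I error is about 7-18% against 4-6% stratified. With a true within-route AUC of 0.70 and a 1 SD shift, pooled power is about 52% to 97% depending on direction, against 87-90% stratified. With failure rates only 10 points apart, false positives stay at about 5-8%.

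The 97% is not a gain, because there the between-route difference is being counted as prognostic value of the index. This is a cheap improvement to stated analyses, not a demonstrated error in the design.

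**What to change.** 1. Include cannulation route (central or peripheral) as one fixed term in the logistic and linear models. In the AIC comparison, put it in both the base model and the base-plus-work model, so that work gets no credit for tracking route.
2. Stratify the log-rank test by route.
3. Report a route-stratified or within-route AUC beside the pooled AUC, labelled descriptive, since about 15 failures per route (as few as 10 in one route at 40/20) cannot support firm estimates.
4. Do not derive separate confirmatory cutoffs per route; they would be too unstable at these counts.

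The cost is some wording and one model parameter against about 30 events. No new data are needed, because route must already be tracked for the balancing step. If the two links turn out weak, little is lost: in the simulations with no shift in work index and a true within-route AUC of 0.70, the stratified test had 88-89% power against 89-90% pooled.

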**Figure 1 F1:**
[figure not shown]
The overview of the study population and the main objectives.

## Statistical analysis

The association of conventional measures of LV function, myocardial work and patient outcome will be assessed by logistic regression, and for certain objectives (ventilator free days, VA-ECMO free days) by linear regression. Despite the limited sample size, a large event rate can be expected in most of the outcome measures, potentially enabling multivariate logistic analyses. Collinearity of variables will be tested at each multivariable model by variance inflation factor (excessive if variance inflation factor >3). To examine the potential added prognostic value of myocardial work to other parameters, the constructed multivariable models will be compared based on Akaike Information Criterion (AIC). Receiver operating characteristic (ROC) curves will be calculated to assess the discriminatory power of the relevant parameters with regards to the study endpoints. Youden index will be used to quantify the optimal cutoff points of each parameter. These cutoff values will be used to dichotomize the study population. Outcomes of the dichotomized groups will be visualized using Kaplan-Meier curves and compared by the log-rank test. All statistical analyses will be performed using SPSS Statistics (IBM Software Group, Armonk NY, USA). A *P*-value of <0.05 will be considered statistically significant.

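### Youden cutoffs are chosen on the outcome and then log-rank tested in the same patients: a useless marker reaches P<0.05 about 20-24% of the time (direction fixed) or 36-39% (direction free), not 5%

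*Protocol article*

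**What the plan says.** The procedure stands in the protocol article, Statistical analysis. After the ROC step, the "Youden index will be used to quantify the optimal cutoff points of each parameter". Next, "These cutoff values will be used to dichotomize the study population". Then: "Outcomes of the dichotomized groups will be visualized using Kaplan-Meier curves and compared by the log-rank test". The section closes with the rule that a P-"value of <0.05 will be considered statistically significant".

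The text gives no split sample, resampling step or adjusted critical value, and it does not call the step exploratory.

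Two other parts of the plan set the scope. The same section opens by assessing association with outcome by logistic regression, and it compares multivariable models by AIC. The Sample size and patient population section gives the planning figures: power was calculated "by assuming an 30% weaning failure rate in a sample size of 100 patients", with 110 to be enrolled to allow for unusable images.

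**The concern.** The Youden index takes the cutoff at which the marker best separates failures from non-failures in the data at hand. The log-rank test then asks whether the two groups differ in those same failures. It is referred to a distribution that is right only if the groups were formed without looking at outcomes. The search over cutoffs is not accounted for, so the test rejects too often. Sensitivity and specificity read off at the chosen cutoff are optimistic for the same reason.

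What is at stake is the truth of any statement that patients below a given value of a work index fared significantly worse, and the accuracy reported for that value. The step is applied to each parameter, so the opportunity for a false positive recurs.

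This is not a detail left to an analysis plan. The article itself fixes the cutoff rule, the population, the test and the threshold.

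**Working it through.** **Inputs**

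- From the article: 100 analysable patients and 30% failures (Sample size and patient population); 110 enrolled; endpoints at 30 days from the start of support (Assessment of endpoints); threshold 0.05 (Statistical analysis).
- Assumed: marker normally distributed and independent of outcome; event times uniform over the window to day 30; non-events censored at day 30; two-sided test on 1 degree of freedom.

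**Procedure for each simulated study**

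1. For every possible cutoff c, compute J(c) = sensitivity(c) + specificity(c) − 1.
2. Take the c that maximises J. *Direction fixed*: low values are declared harmful in advance. *Direction free*: the data decide, either by the side of 0.5 on which the AUC falls or by the larger |J|.
3. Split the same patients at c and compute the log-rank statistic (O − E)²/V. Reject if it exceeds 3.84, the 5% point of chi-square on 1 degree of freedom.

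**Control: is the plan's own 5% reproduced when the cutoff ignores the outcome?** Yes. With a median split, 18 settings (100 or 110 patients; 30%, 50% or 60% events; 4,000 runs each) gave 4.1% to 5.7%, mean 4.9%. The standard error of one setting is √(0.05 × 0.95 / 4,000) = 0.3 percentage points. The test itself is sound, and the excess below comes from the cutoff search.

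**Planned procedure, 100 patients, 30% events, useless marker**

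| Simulation runs | Direction fixed | Direction free |
|---|---|---|
| 3,000 | 20% | 37.5% |
| 4,000 | 21% | 38% |
| 4,000 | 22.3% | 37.5-37.8% |
| 5,000 | 23% | 39% |
| 10,000 | 22.8% | 37.4% |

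For the largest simulation the standard error in the fixed case is √(0.228 × 0.772 / 10,000) = 0.4 percentage points. The mean apparent Youden index, which should be near zero for a useless marker, is about 0.13 with direction fixed and 0.18 with direction free.

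**Sensitivity to assumptions**

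- Sample size and event rate matter little. Across 100 or 110 patients and 30% to 60% events, the rates are 21-24% (fixed) and 36-38% (free, by AUC). Taking the larger |J| gives 36-40%.
- Restricting the search reduces the excess but does not remove it. At 100 patients and 30% events, cutoffs within the central 80% of the marker give 19.3% and 36.7%, and within the central 60% they give 15.3% and 30.2%. The article states no such restriction.

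**What would hold 5%.** With 100 patients and 30% events, the log-rank chi-square after a Youden search would have to exceed about 7.7 (nominal P about 0.005) with direction fixed, or about 9.0 (nominal P about 0.003) with direction free. The plan uses 3.84.

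**Contrast with the continuous marker.** In the same kind of null data, a two-sample t-test on the undivided marker, standing in for logistic regression, rejected in 5.5%.

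The stated 92.2% power plays no part in this check.

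**The case against.** The best case on the other side is that the log-rank test is not where the plan's main inference lies. Association is assessed by logistic regression, added value by AIC and discrimination by ROC curves. Cutoffs enter only after the ROC step, and nothing says that markers are dichotomised for the regressions. The main objective in Assessment of endpoints is superiority over conventional LV measures, and a log-rank test between two groups split on one marker does not compare markers. All of this stands, and it limits the point.

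Three stronger readings are therefore tempting but unsupported:

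- A reader might infer that the study's main analysis is invalid, or that the Kaplan-Meier comparison is its principal result. The document supports neither.
- A reader might infer that the cutoffs will fail to replicate. The simulation covers only a marker with no association and says nothing about a cutoff's stability when the marker is prognostic. The supportable statement is that they may be unstable and that their apparent accuracy is optimistic.
- A reader might take the percentages as the share of studies that go wrong. They apply per marker and per log-rank test. No study-wide figure is given, because the markers are correlated to an unknown degree.

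Direction matters too. The two clinical examples in Assessment of endpoints treat a higher GWI as favourable, so the lower range is the relevant one for GWI. The direction is less explicit for the other indices.

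It can also be said that optimism correction and exploratory labelling are usually left to an analysis plan. That is fair for those items. It does not answer the uncorrected P-value, which the article prescribes.

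**Conclusion.** The point holds for the dichotomised results. The prescribed log-rank P-value has a false-positive rate per marker of about 20-24% with direction fixed and about 36-39% with direction free, roughly four to eight times the stated 5%. The apparent sensitivity and specificity at the same cutoffs are optimistic. The logistic regression and the AIC comparison are not inflated by this step.

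The size rests on a marker unrelated to outcome, an unrestricted cutoff search, the protocol's planning figures and an assumed shape of event times. Confining cutoffs to the central 60% of the marker still leaves about 15% and 30%.

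**What to change.** 1. State that inference on each marker rests on the planned logistic regression with the marker kept continuous. This is the natural reading already and needs only a sentence.
2. Draw and test the Kaplan-Meier curves at a split fixed before outcomes are seen, for example the median.
3. If Youden cutoffs are kept, present them as exploratory, with bootstrap optimism-corrected sensitivity and specificity. Replace the ordinary log-rank P-value with one from a permutation or maximally selected rank test, or give no P-value.

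The change should be made before outcomes are analysed, since a split chosen afterwards is no longer pre-specified. Enrolment, procedures and data collection are untouched. The costs are less striking curves and, for the corrected P-value only, possibly software beyond SPSS, to which the section commits all analyses. The pre-fixed split needs no new software.
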